#### Secondary

Subjects will be asked to complete two questionnaires, specifically, the MOS Short Form 36-item (SF-36) (Korean version) and the Measure Yourself Medical Outcome Profile (MYMOP2). These surveys were selected based on the aims of the trial and on their clinical relevance and feasibility. The SF-36 is a widely used, reliable, valid and responsive measure of outcome health survey. The SF-36 consists of eight scales: physical function, role-physical, bodily pain, general health, mental health, role-emotional, social function, and vitality.

The MYMOP is a patient-generated outcome questionnaire, which is problem-specific but includes general well-being. MYMOP aims to measure the outcomes that the patient considers to be most important. MYMOP is applicable to all patients who present with symptoms; these symptoms can be physical, emotional or social [19].

Heart rate will be assessed on every visit, and questionnaires will be administered at weeks 0, 4 and 8. Changes in norepinephrine, cortisol, renin, angiotensin, total cholesterol, and triglycerides will be examined through blood tests at weeks 0 and 8. Blood samples will be taken in the morning after an overnight fast to achieve standard conditions with respect to dietary intake.

#### Follow-up

Four weeks after completion of the 8 weeks of qigong exercise, blood pressure, heart rate, and the SF-36 and MYMOP2 questionnaires will be evaluated. The follow-up assessment is designed to evaluate the long-term effect of qigong exercise.

#### Data analysis

Collected data will be recorded on standardized forms. Descriptive statistics will be calculated for dependent and independent variables. This analysis will include summary statistics of demographic information and outcome measures.

The primary analysis of the data will be undertaken using the principle of intent-to-treat (ITT). Our ITT analysis will include all participants, including those who are not fully compliant and those missing outcome data. We will evaluate the effectiveness of qigong exercise and no treatment on blood pressure at 8 weeks using an analysis of covariance (ANCOVA).

Demographic and clinical characteristics of subjects in the qigong and the non-treated group will be compared upon admission using a 2-sample t-test (continuous data) and chi-square analysis (normal data). Nonparametric methods will be used when assumptions of normality are violated. To control for baseline differences between groups, variables that are significantly different at baseline will serve as covariates in the analyses. Data will be analyzed on an intention-to-treat basis. Software will include the Access and SAS version 9.1 programs. The alpha level will be set at < 0.05.

Adverse events will be reported to the data and safety monitoring board. Adverse events will be recorded when participants present with complaints at any time and will be based on the questioning of participants. Serious adverse events will be recorded as required by the International Conference on Harmonization Guideline E2A. We will submit the results of the trial for publication in an appropriate journal irrespective of outcome. We will report the trial in accordance with the CONSORT statements.

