#### Sample size

There are no previous clinical trials to evaluate the effect of qigong on pre- or mild hypertension. Therefore, this study is designed as a pilot study to calculate the appropriate sample size for future randomized clinical trials. Each group will include 20 participants, which is the minimum sample size for evaluating the effect of qigong [17,18].

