#### Randomization and allocation concealment

The subjects admitted to the trial will be randomized to either the qigong group or the non-treated group. Participants will be randomized before the first treatment by an online centralized randomization service. Randomization will be stratified by age and sex.

Allocation concealment will be ensured, as the service will not release the randomization code until the patients are recruited into the trial after all baseline measurements are completed.

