## Discussion

The primary end point for this study is the change in patient blood pressure from baseline to 8 weeks post-therapy. Eight-week changes in hormone levels and health status, as measured by SF-36 and MYMOP2, are secondary end points. The primary comparison is between participants randomly assigned to qigong exercises versus no intervention. Subgroup analyses for age, gender and baseline BP will be conducted by including each classification.

Many qigong researchers consider that the qigong effects on the human body are systemic without targeting one particular element, such as BP [7]. Therefore, we will use the MYMOP 2 and the SF-36 questionnaires, which can measure the quality of life, health status and the severity of subjective symptoms, as outcomes for this study.

The standard mercury sphygmomanometer is the most common device used to measure blood pressure [2]. The accuracy of automatic blood pressure measurement is still controversial [20,21]; therefore, the mercury sphygmomanometer is considered to be the 'gold standard' for measuring blood pressure. To avoid the white-coat effect [22], the CRC will not wear a white coat during this clinical study.

This study will be the first randomized trial to investigate the effectiveness of qigong exercises for the treatment of pre- and mild hypertension. The main focus of this trial is to investigate the role of qigong in reducing the blood pressure of patients with pre- or mild hypertension. This trial will contribute information needed to begin answering important clinical questions regarding the effects of qigong in lowering the blood pressure of patients with pre- and mild hypertension. Although the trial is not sufficiently powered to determine the effectiveness of qigong on hypertension, we will compare the effect size between groups in order to form larger-scale trials in the future.

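### The only covariate rule for the primary ANCOVA is a baseline significance screen, so neither baseline blood pressure nor the stratification factors are fixed in the model

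*Protocol article*

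**What the plan says.** Under Data analysis, the protocol article evaluates the effect "on blood pressure at 8 weeks using an analysis of covariance (ANCOVA"). It names no covariate for that model. The next paragraph says that demographic and clinical characteristics "will be compared upon admission using a 2-sample t-test (continuous data) and chi-square analysis (normal data"), with nonparametric methods if normality fails. It then gives the rule: "To control for baseline differences between groups", "variables that are significantly different at baseline will serve as covariates in the analyses". On the level it says only "The alpha level will be set at < 0.05".

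Under Randomization and allocation concealment: "Randomization will be stratified by age and sex". Neither factor is placed in the primary model. The Discussion mentions age, gender and baseline BP only as subgroup factors, and describes the endpoint as a change: "The primary end point for this study is the change in patient blood pressure from baseline to 8 weeks post-therapy".

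**The concern.** Allocation is central and concealed, so any baseline difference between the groups is due to chance. A significance test on such a difference shows how unusual the chance result is. It says nothing about whether the variable predicts week-8 BP, which is what makes a covariate worth including. Baseline BP is likely to be the strongest predictor, yet the written rule admits it only after an unusual draw. Age and sex are balanced by design, so they should hardly ever pass; if they predict BP, leaving them out makes the standard error too large.

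Three things are at stake: precision in a trial of 40 people, the accuracy of the effect size given the imbalance that actually occurs, and a primary model that is known before the data are seen. The second matters because the stated purpose is to size future trials.

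**Working it through.** **Inputs from the protocol article.** 20 per group (Sample size); alpha 0.05, taken as two-sided; the covariate rule and the ANCOVA (Data analysis); stratification by age and sex. The sample size rests on citations, with no effect, SD or power given, so there is no planned figure to reproduce.

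**Assumptions, none from the document.** Normal BP with equal SD at baseline and week 8; correlation r between them of 0.4 to 0.7; true effect 0.8 SD. Where baseline BP is not significant, the literal reading is taken to mean a comparison without it.

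**1. How often the factors enter.** Under randomisation a test at 0.05 is significant in 5% of trials, so baseline BP is left out in about 95%. For age and sex, 20,000 trials were simulated with assumed strata (age cut at 45, sex 50:50, blocks of 4). Sex was significant in none and age in 0.1%.

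**2. Precision.** In units of the BP variance, the outcome variance behind the group comparison is 1 for week-8 BP alone, 2(1 − r) for change, and 1 − r² for ANCOVA with baseline. At r = 0.6 these are 1, 0.80 and 0.64. ANCOVA is smallest for every r strictly between 0 and 1.

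**3. Power by simulation.** The rule is: test baseline BP at 5%, use ANCOVA if significant, otherwise leave baseline BP out.

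| r | Baseline always in | Rule, week-8 BP | Rule, change |
|---|---|---|---|
| 0.4 | 76% | 70% | 62% |
| 0.5 | 80% | 70% | 70% |
| 0.6 | 86% | 70-71% | 79% |
| 0.7 | 92% | 71% | 89% |

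The loss runs from 6 to 21 points for week-8 BP and from 14 down to 3 points for change.

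**4. Type I error.** With no true effect, the rule rejects in about 3.7-4.6% of trials over the same correlations, against about 5% with baseline always in the model.

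**5. Imbalance that passes the screen.** The largest non-significant gap is t(0.975; 38) × √(2/20) = 2.024 × 0.316 = 0.64 SD. A gap g shifts the week-8 comparison by r × g and the change comparison by (r − 1) × g. At r = 0.6 and an assumed SD of 10 mm Hg, the edge case is g = 6.4 mm Hg:
- week-8 BP: 0.6 × 6.4 = 3.8 mm Hg
- change: −0.4 × 6.4 = −2.6 mm Hg, the opposite direction

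A typical absolute gap is 0.8 × √(2/20) = 0.25 SD, or 2.5 mm Hg. The shifts are then 0.6 × 2.5 = 1.5 and −0.4 × 2.5 = −1.0 mm Hg.

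**6. Irrelevant covariates.** If k independent variables are tested, the chance that at least one is significant is 1 − 0.95^k: 40% for k = 10, 54% for 15 and 64% for 20. The listed variables include weight, waist and hip circumference and body fat, which are plainly correlated, so these figures overstate the chance.

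**The case against.** The strongest reply is that the plan commits to an ANCOVA without condition, and an ANCOVA needs a covariate. The obvious one is baseline BP. The significance rule stands in the following paragraph and may only add to it. This is a fair reading, and under it the power and BP bias figures do not apply. But the text does not say so, and that reading leaves the screen in force and age and sex out of the model.

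Other points limit the concern:
- A reader might infer that chance imbalance is left wholly uncorrected. The stated endpoint is a change, which brings in baseline BP by subtraction. Imbalance is then over-corrected, and at high correlation the power loss is small. Imbalance stays uncorrected only if week-8 values are compared without baseline BP.
- A reader might infer extra false positives. The departure from 5% is downward.
- The 3.8 and 2.6 mm Hg shifts are edge cases. The bias is conditional on the observed imbalance and averages to zero over randomisation. The 2.6 mm Hg is below one standard error of the change comparison, 10 × √0.8 × √(2/20) = 2.8 mm Hg.
- An irrelevant covariate costs about one degree of freedom and causes no bias. The rule uses baseline data only, so outcomes cannot steer it.
- The trial is a pilot that declares itself underpowered.

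All of these stand as limits on size. None justifies the rule. Pilot status does not remove the point either, because the effect size is meant to inform larger trials. Nor can the rule be treated as detail left to an unseen analysis plan, since the article states it.

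**Conclusion.** The point holds as a should-fix. The only stated way for a covariate to enter the primary model is a test that measures chance, and neither baseline BP nor the stratification factors are fixed in the model.

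If baseline BP is not otherwise included, power is 70-71% (week-8 BP) or 62-89% (change), against 76-92% with baseline BP always in. This rests on the assumed effect of 0.8 SD and correlations of 0.4 to 0.7. Baseline gaps up to 0.64 SD then stay in the week-8 comparison or are over-corrected in the change score. Type I error is conservative. The harm is lost precision, conditional bias in the effect size passed on, and a model not fixed in advance. If ANCOVA was meant to include baseline BP, what remains is the screen and the omission of age and sex.

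A must-fix rating is not supported: the text allows the milder reading, false positives are not increased, and the trial makes no claim to adequate power.

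**What to change.** Delete the significance-based covariate rule. State instead that the primary ANCOVA regresses week-8 BP on treatment group, the baseline value of the same BP measure, and the stratification factors age and sex, whatever baseline differences are observed. With baseline in the model, the treatment estimate is the same whether the outcome is written as week-8 BP or as change, so this wording also fits the stated endpoint.

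All the variables are already collected. The cost is one sentence, written before the data are unblinded, and about three degrees of freedom (38 residual falling to 35 if age and sex take one each). Dropping the baseline tests from the report is optional; what matters is that they no longer choose the model.

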#### Blinding

Outcome assessors will be blind to group allocation and will not be involved in providing intervention. However, it will be difficult to blind the participants because the control group will not receive any intervention.

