### Intervention

#### Qigong exercise

Although there have been several qigong trials for hypertension, the type of qigong used in those trials was diverse, and there has been no standardized qigong exercises for the treatment of hypertension. We have developed a qigong protocol for the treatment of hypertension based on discussions with three qigong professionals.

Qigong will be taught by an instructor with expertise in qigong. The participants will visit the clinic and take 3 qigong classes per week for 8 weeks. Each qigong class lasts 30 minutes, including a warm-up (5 min) and a cool-down (5 min) portion. In addition, the subjects will be asked to practice qigong at home for 30 min more than 2 times a week for the duration of the study. The purpose of qigong exercise is to improve kidney and liver function, to improve blood circulation and to lower blood pressure through calming (Table 2).

**Table 2 T2:** Composition of Qigong

Stage	Stage	Motions
Warm-up	1	Meditate for 1 minute, swing your arms and shoulders and flex your waist, knees and ankles.
1^st^	1	Lift both hands overhead, locking your fingers together while bending and extending your knees.
	2	Lean your body to the right while breathing in, and stand straight, while breathing out. Repeat 4 times to the left and right, alternating.
2^nd^	1	Advance your left foot, and lower your right hand from the left of your head to your right leg drawing an oblique line quickly. Repeat this 8 times to the left and right, alternating.
3^rd^	1	Advance your right foot, lift your right arm and support your right elbow with the back of your left hand.
	2	Lower your body quickly while bending your knees and clenching your right fist. Repeat this 8 times to the left and right, alternating.
4^th^	1	Advance your left foot and put your left hand on your left knee. Put your right hand on your left hand and push down as much as possible. Lift up right hand to the right. Repeat this 8 times to the left and right, alternating.
5^th^	1	Put your feet apart and relax your wrists and lift your hands slowly forward.
	2	Lower your hands while bending your knees. Repeat this 10 times.
6^th^	1	Support your back with your hands and lean back.
	2	Bend your waist forward and sweep the back of your legs with your hands.
	3	With straight waist, lift your hands overhead while breathing in and lower them, while breathing out. Repeat this 8 times.
7^th^	1	Put your feet apart and twist your body backward to the left.

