#### Non-treated group

The control group will receive no instruction in qigong exercise. They will be asked to maintain their routine lifestyle, including diet, exercise, work and other activities.

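### Adverse-event recording has no stated arm-equal timing, and the qigong arm has 24 class contacts that controls lack, so any by-arm adverse-event summary risks differential ascertainment

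*Protocol article*

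**What the plan says.** The rule is in the Data analysis section of the protocol article: "Adverse events will be recorded when participants present with complaints at any time and will be based on the questioning of participants". Events are then reported to the data and safety monitoring board. The rule has two routes: a participant comes forward with a complaint, or is asked. No schedule, wording or look-back period is given for the asking, and neither route is restricted to one arm.

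Contact differs between the arms:

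- **Qigong** (section Qigong exercise): "The participants will visit the clinic and take 3 qigong classes per week for 8 weeks".
- **Control** (section Non-treated group): "The control group will receive no instruction in qigong exercise". Participants are asked to keep their usual lifestyle, and no visits of their own are described.
- **Both arms, by inference** (sections Secondary and Follow-up): "Heart rate will be assessed on every visit, and questionnaires will be administered at weeks 0, 4 and 8"; and "Four weeks after completion of the 8 weeks of qigong exercise, blood pressure, heart rate, and the SF-36 and MYMOP2 questionnaires will be evaluated", which is week 12. Neither sentence limits these assessments to one arm.

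On masking, the Blinding section states: "Outcome assessors will be blind to group allocation and will not be involved in providing intervention". Of participants it states that "it will be difficult to blind the participants because the control group will not receive any intervention". It does not say who collects adverse events.

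**The concern.** A rule that records complaints when participants bring them depends on how often they have someone to bring them to. One arm meets staff three times a week for eight weeks, while the other may meet them only twice in that period. A minor ache or dizzy spell is more likely to be mentioned at a class a day or two later than at an assessment up to four weeks later. Participants also know their allocation, so those who exercise may be readier to mention aches.

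At stake is how adverse-event counts by arm are read. With equal true risk, the rule would tend to show more events with qigong. The monitoring board and later readers could not separate an effect of the exercise from an effect of contact. One aim of the pilot is to test the methods for larger trials, so an uneven capture rule could be carried forward. Unequal capture cannot be repaired once the data are collected.

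**Working it through.** The article gives no adverse-event rate and no safety sample size, so there is no figure of its own to reproduce. The check has two parts.

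**1. Contacts, from the article**

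- Qigong classes: 3 per week × 8 weeks = 24. Control classes: 0.
- Shared assessments after baseline: weeks 4 and 8, and week 8 + 4 = 12.
- During treatment: qigong 24 (assessments on class days) to 24 + 2 = 26 (separate days); control 2. Ratio 24/2 = 12 to 26/2 = 13.
- Through week 12: qigong 25 to 27; control 3. Ratio 25/3 = 8.3 to 27/3 = 9.

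The control counts assume that controls attend exactly the shared assessments. The article implies this but does not list their visits.

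**2. What this could do to recorded events (assumed inputs)**

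None of these assumptions comes from the documents:

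- the true risk of a minor complaint is 5% per week in both arms, independent between weeks;
- every such complaint in the qigong arm is captured at a class;
- controls are questioned at weeks 4 and 8 only, recall the last *r* weeks, and report nothing between visits.

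Share with at least one recorded event over 8 weeks:

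- Qigong: 1 − 0.95^8 = 33.7%, or 6.7 of 20.
- Control: 1 − 0.95^(2*r*).

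| Control recall *r* | Control share | Expected of 20 | Apparent ratio |
|---|---|---|---|
| 1 week | 1 − 0.95^2 = 9.75% | 1.95 | 3.45 |
| 2 weeks | 1 − 0.95^4 = 18.5% | 3.7 | 1.81 |
| 3 weeks | 1 − 0.95^6 = 26.5% | 5.3 | 1.27 |
| 4 weeks (full) | 1 − 0.95^8 = 33.7% | 6.7 | 1.00 |

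A simpler version sets recorded risk = true risk × detection. With detection of 0.9 in the qigong arm and 0.9, 0.7, 0.5 or 0.3 in controls, the apparent ratio is 1.0, 1.29, 1.8 or 3.0 at any common true risk. At a true risk of 20% the expected counts are 3.6 of 20 with qigong against 3.6, 2.8, 2.0 or 1.2 of 20.

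Both versions show the same thing: the distortion disappears when detection is equal and grows as control detection falls. Any reporting by controls between visits moves the ratio back towards 1.0.

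**The case against.** The strongest case against has five parts.

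- **No safety comparison is planned.** Adverse events are not a primary or secondary endpoint, and no between-arm test of them is stated. This stands. A reader might infer that a planned safety analysis is biased, but the article contains none. The point concerns any by-arm summary made from these data. Such a summary is foreseeable, since events go to a monitoring board and the trial is to be published.
- **The rule includes questioning, and reporting is open at any time.** This also stands. A reader might infer that controls are never asked or cannot report between visits, and the text does not say so. Questioning equalises capture only if its timing and look-back are the same in both arms, which the article does not fix. Even then, the volunteered route would add mainly to the qigong count.
- **An article leaves form and script details to the full protocol.** This is true of the wording and the form, and the full protocol may already schedule equal questioning. But the article is not merely silent: it states a capture rule that includes volunteered complaints, alongside very unequal contact.
- **The magnitude is assumed.** This stands. The risk, recall and capture inputs are not in the documents, and the range must start at 1.0. Even the extreme case is about 7 against 2 of 20, with a two-sided Fisher p of about 0.13, so it would affect the reading of a table rather than produce a significant test.
- **Having the blinded assessor ask could unmask allocation.** This stands and shapes the fix. A complaint about a class would reveal the arm to the person whose blinding protects the primary outcome.

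**Conclusion.** The point holds as a risk of differential ascertainment. Followed as written, the rule would probably inflate the recorded event rate in the qigong arm relative to controls. The contact imbalance of 24 classes against none follows directly from the article. The effect on event counts does not: it depends on recall, on reporting between visits and on when questioning takes place. Under the assumptions shown, the apparent ratio lies between 1.0 and about 3.45.

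A reader might go further and infer that equal true rates are bound to appear as an excess with qigong, or that the excess is at least 1.8-fold. The documents do not support either. Equal questioning with full recall gives no excess, and nothing in the article rules that out.

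The blood pressure, hormone and questionnaire analyses are not affected. This is a modest point for a 40-person pilot, but worth settling before enrolment.

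**What to change.** 1. Put the same scripted adverse-event question, covering the whole interval since the last assessment, to both arms at weeks 4, 8 and 12.
2. Have it asked by a staff member other than the blinded blood pressure assessor, or only after blood pressure has been measured and recorded.
3. Base any between-arm adverse-event summary, including one for the monitoring board, on these answers alone.
4. List events volunteered at classes or between visits separately, by arm and by how they came to light.
5. Leave serious-event reporting unchanged.

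If the full protocol already contains such a schedule, it is enough to say so where the rule is stated.

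The cost is a short question at assessments already planned, and possibly a second staff member for a few minutes. The downside is that minor events mentioned only at classes leave the comparison, though they are still listed. In the illustration, if qigong participants recalled only one or two weeks, the comparison would count about 2 to 3.7 of the 6.7 participants with an event, and the ratio would return to 1.0. The change equalises the opportunity to report. It does not remove any difference in readiness to report among participants who know their allocation.
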